### Statistical analysis

We will perform a per-protocol analysis and an intention-to-treat analysis. Only participants who complete treatment will be included in the per-protocol analysis, whereas all of the participants who receive at least one tDCS session will be included in the intention-to treat-analysis. A last-observation-carried-forward approach will be adopted for the analysis of outcome data. The mean score of the FSS will be calculated. The sum of individual item scores will be computed for the MFIS and the total score and physical, cognitive and psychosocial subscores will be derived. Demographic characteristics will comprise age, sex, and scores on the Chinese version of the GDS, the Chinese version of the HADSA, the PASE, the BI, the PSQI, and the NIHSS, and the severity of PSF will be measured using the FSS and the MFIS. Chi-square tests (for categorical variables such as sex) and t-tests (for continuous variables such as age) will be used to compare baseline performance. The effects of tDCS upon completion of treatment (T1) will be studied by entering the participants’ scores on the MFIS (total score and subscores) into a mixed-model analysis of variance with baseline MFIS scores as covariates, and the tDCS intervention (T0, T1) and stimulation (active, sham) as between-participant factors. The trend of tDCS effects will be studied by entering the participants’ scores on the MFIS (total score and subscores) into a linear mixed model with the tDCS intervention (T0, T1, T2, T3 and T4) and stimulation (active, sham) as within-participant factors. Pairwise comparisons between baseline and individual post-measurement-day significant results will conducted using Bonferroni t-tests for related samples. Withdrawals will be analyzed by logistic regression. The level of significance will be 0.05.

The safety analysis will be descriptive and exploratory. Key safety measures will be based on the tDCS AEs questionnaire and include the overall incidence and intensity of AEs; the number of AEs leading to treatment discontinuation; skin reactions; and other AEs.

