### Withdrawal criteria

The participants should be able to complete the 10 sessions of tDCS treatment within 1 week. If they miss a scheduled session, they can receive another session when convenient. If the participants cannot complete the 10 sessions, they will be regarded as dropouts. In addition, participants will be removed from the study if they (i) withdraw their consent for tDCS treatment and/or (ii) have a severe AE that may lead to significant distressful consequences (seizure, skin burn or blister).

We will continue to follow withdrawn participants and perform outcome measures as far as possible.

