### Sample size estimates

Statistical power was computed using Power Analysis & Sample Size 2005. We assumed that the standard deviation of the MFIS score at baseline will be 3.9 (60), that the sham stimulation will not cause any change in fatigue and that a decrease of at least 3.0 MFIS points will be clinically relevant (36). Hence, the effect size of tDCS will be (3.0/3.9 = 0.77). Given that such a large effect size is unusual in clinical contexts, we will instead use a more realistic effect size, i.e., 0.50. One pairwise comparison will be performed in the analysis of variance. A sample size of 63 per group (a total of 126 participants) will give rise to 80% power in identifying the main effect of tDCS (73). Thus, assuming a dropout rate of 20%, 156 (126/0.8) participants will be recruited.

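### Last-observation-carried-forward is fixed as the rule for all outcome data; depending on when participants are lost, it can shrink a real effect at T1 or leave a false one at T4

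*Protocol article*

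**What the plan says.** Under Statistical analysis, the protocol article says "A last-observation-carried-forward approach will be adopted for the analysis of outcome data". The sentence is not limited to a visit, an outcome or an analysis set, and no other treatment of missing outcomes is given.

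Four other statements bear on it:

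- **Analysis set.** Under Statistical analysis, "all of the participants who receive at least one tDCS session will be included in the intention-to treat-analysis". A participant can therefore be in this set with a T0 score and nothing later.
- **Models.** The T1 comparison takes baseline MFIS as a covariate: "The effects of tDCS upon completion of treatment (T1) will be studied by entering the participants’ scores on the MFIS". The trend is studied in a linear mixed model over T0 to T4.
- **Follow-up.** Withdrawal criteria counts those who do not complete the ten sessions as dropouts, but adds: "We will continue to follow withdrawn participants and perform outcome measures as far as possible".
- **Planned loss.** Sample size estimates works with "assuming a dropout rate of 20%, 156 (126/0.8) participants will be recruited".

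Primary outcome measure gives the MFIS a recall window that changes by visit: 4 weeks at T0, 1 day at T1, 1 week at T2 and T3, and 2 weeks at T4.

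**The concern.** Carry-forward assumes that a participant's fatigue stays where it was last measured, and it then treats the filled value as if it had been observed. In this trial that has two consequences.

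At T1 the only earlier score is T0, so carry-forward assigns exactly zero change. If active stimulation works, this pulls the estimated difference toward zero.

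From T2 to T4 the question is whether an effect lasts. Holding a T1 score constant to T4 builds persistence into the data of everyone lost after T1. If the effect wanes, part of the T1 difference is reported at T4 although it is no longer there.

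The recall windows add to the difficulty. A T0 score carried to T1 puts a 4-week recall in place of a 1-day recall. A T1 score carried to T4 puts a 1-day recall in place of a 2-week one.

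The rule is also unnecessary. A linear mixed model uses incomplete series without imputation, and the protocol already intends to keep measuring withdrawn participants.

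**Working it through.** **Inputs from the protocol**

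- Effect size: "we will instead use a more realistic effect size, i.e., 0.50" (in SD units).
- Baseline SD of the MFIS 3.9, and no change under sham (Sample size estimates).
- 63 per group for 80% power; 156 recruited, 78 per group.
- Dropout 20%.
- "The level of significance will be 0.05"; sidedness is not stated.

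**Assumed, because the protocol does not give them:** when participants are lost, the split by arm, whether the effect wanes, and the correlation between visits (0.3 to 0.7).

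**Step 1. The plan's own figure.** The normal approximation for two means with d = 0.50, two-sided 0.05 and 80% power gives 63 per group, as stated. (One-sided would give 50, so two-sided is implied.) Power at 63 is 80.1% by that approximation and 79.5% by the t-test. The inflation 126/0.8 is 157.5, against the stated 156, a difference of no weight here.

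**Step 2. Loss before T1.** Let s be the sham improvement, D the added active effect, and dA and dS the shares of the active and sham arms lost before T1. Under carry-forward:

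T1 difference = (s + D)(1 − dA) − s(1 − dS)

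With s = 0 this reduces to D(1 − dA):

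| Lost before T1 | Estimated difference | Bias |
|---|---|---|
| 5% | 0.50 × 0.95 = 0.475 SD | −0.025 SD |
| 10% | 0.50 × 0.90 = 0.45 SD | −0.05 SD |
| 20% | 0.50 × 0.80 = 0.40 SD | −0.10 SD (0.10 × 3.9 = 0.39 points) |

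With D = 0 and dA = dS = d, the expression is s(1 − d) − s(1 − d) = 0, so there is no bias.

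**Step 3. Power at T1.** The planned T1 analysis adjusts for baseline. In simulations of a baseline-adjusted comparison (78 per arm, 20% lost before T1 completely at random, true effect 0.50 SD):

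| Correlation | Carry-forward | Observed data only |
|---|---|---|
| 0.3 | 78% | 83% |
| 0.5 | 87% | 90% |
| 0.7 | 96% | 97% |

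The loss is about 1 to 5 points. The estimate is distorted more than the power.

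**Step 4. Loss after T1.** Suppose nobody is lost before T1, sham does not change, and the active effect is D at T1 and zero at T4. If a share q of the active arm is lost after T1, then under carry-forward:

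T4 difference = q × D

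- q = 20%: 0.20 × 0.50 = 0.10 SD, or 0.39 MFIS points.
- q = 10%: 0.10 × 0.50 = 0.05 SD, or 0.05 × 3.9 = 0.195 points.

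**Step 5. False-positive rate at T4.** For the baseline-adjusted between-arm comparison at 0.05, with 78 per arm and equal random loss after T1:

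- 20% lost: about 9 to 15% rejections over correlations 0.3 to 0.7 (12.1% at 0.6), against about 5% on observed data (4.9% at 0.6).
- 10% lost: about 6 to 7%. With a further 10% lost before T1 it is 6.9% at correlation 0.6.

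**The case against.** The strongest reply is that the planned 20% need not mean 20% missing MFIS scores. In this protocol a dropout is someone who does not complete the ten sessions, and such people are still to be measured where possible. Treatment lasts five days, missed sessions can be made up, and T1 falls one day after the last treatment day. Loss of all 20% before T1 is therefore a worst case. It also cannot occur together with loss of 20% after T1, because these would be the same participants. All of this stands. It lowers the likely size but leaves the rule in place.

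The protocol also plans a per-protocol analysis, which is less exposed to a T0 score carried to T1, and a logistic regression of withdrawals. Neither replaces carry-forward in the intention-to-treat analysis. The T4 rejection rates are for a between-arm comparison at that visit. The protocol names a longitudinal model and Bonferroni-corrected paired comparisons with baseline, so the rates illustrate the distortion and are not the error rate of a named test.

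Three stronger readings are tempting, and the documents do not support them:

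- **Power falls to 70%.** That is the figure for an unadjusted t-test at 0.40 SD with 78 per arm. The planned T1 analysis adjusts for baseline, and there the loss is about 1 to 5 points.
- **Carry-forward favours active stimulation at T1.** With sham unchanged, as the protocol assumes, the bias is toward no effect. It can run the other way only if sham participants improve and more of them are lost.
- **Carry-forward inflates the type I error at T1.** If both arms improved by 0.5 SD and losses were 30% against 10%, there would be a false 0.10 SD difference and about 13% rejections. Its direction depends on which arm loses more. Neither the split nor the sham response is in the protocol, and Sample size estimates assumes no sham change.

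**Conclusion.** The point holds in a conditional form. Carry-forward is the stated rule for the primary outcome, and its bias has no fixed direction: the same rule can shrink a real effect at T1 and keep alive a vanished one at T4. It therefore cannot be defended as simply conservative.

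The size is modest. It is at most 0.10 SD in either direction when the whole planned 20% is lost equally in both arms on one side of T1, with a 0.50 SD effect and no sham change, and about half that at 10%. The T4 artefact needs both loss after T1 and a waning effect; the figures above take complete waning. The comparison with observed data assumes random dropout.

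This should be corrected before unblinding, since a later change could look driven by the data. It does not by itself invalidate the trial.

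**What to change.** Replace the carry-forward sentence with this: MFIS will be analysed by a likelihood-based mixed model of all observed T1 to T4 scores, including those collected after withdrawal from treatment, with baseline MFIS as covariate, stimulation as a between-participant factor, visit, and a stimulation-by-visit interaction. The T1 contrast and the later contrasts then come from one model. The present trend model lists stimulation as a within-participant factor, so that wording must change at the same time.

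Keep carry-forward at most as a labelled sensitivity analysis. A delta-shift sensitivity analysis for data not missing at random is optional.

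The cost is a rewritten sentence or two and a small amount of extra analysis, with no new data. The main analysis would rely on missing at random, and participants with only a T0 score would contribute no outcome, which makes the promised follow-up after withdrawal more important.

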**Methods and design:**

This proposed project will be a double-blind randomized control trial. The participants will be randomly divided into two groups. The control group will receive sham tDCS, and the treatment group will receive active tDCS. The latter treatment will involve application of a constant 2-mA current via one 5 × 5-cm anodal electrode positioned on the scalp over the C3 or C4 positions (motor cortex) of the lesioned hemisphere and one cathodal electrode positioned at the ipsilateral shoulder in two 20-min sessions per day for 5 days. The period of follow-up will be 4 weeks.

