### Primary outcome measure

The MFIS will be administered before treatment (T0), after 10 treatment sessions (T1, 1 day after the fifth treatment day), and 1 week (T2), 2 weeks (T3) and 4 weeks (T4) thereafter (36), at the same time of day. The time window of administration will be adjusted to assess changes between time points (4 weeks for T0, 1 day for T1, 1 week for T2 and T3, and 2 weeks for T4). The participants and the research assistant who administers the MFIS will be blinded to the delivered treatment.

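### Both MFIS models give one factor the wrong label, and the T1 model uses baseline as covariate and outcome with no term named as the treatment effect

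*Protocol article*

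**What the plan says.** All references are to the protocol article.

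- **T1 model (Statistical analysis).** MFIS scores go "into a mixed-model analysis of variance" "with baseline MFIS scores as covariates, and the tDCS intervention (T0, T1) and stimulation (active, sham) as between-participant factors".
- **Trend model (Statistical analysis).** MFIS scores go into a linear mixed model with "the tDCS intervention (T0, T1, T2, T3 and T4) and stimulation (active, sham) as within-participant factors". No baseline covariate is stated here.
- **Design (Abstract, Methods and design).** "The participants will be randomly divided into two groups". "The control group will receive sham tDCS, and the treatment group will receive active tDCS".
- **Measurement (Primary outcome measure).** "The MFIS will be administered before treatment (T0), after 10 treatment sessions (T1, 1 day after the fifth treatment day", with T2, T3 and T4 following in the same participants.
- **Power (Sample size estimates).** An effect size of 0.50 is used, and 63 per group "will give rise to 80% power in identifying the main effect of tDCS".

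The Statistical analysis section does not say whether the treatment effect is the stimulation main effect or the time-by-stimulation term. The only follow-up comparisons it names are Bonferroni-corrected paired tests of baseline against later visits, which do not compare the arms.

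**The concern.** In a parallel-group trial with repeated measurements, stimulation varies between people and time varies within them. Each model puts both factors under one label, so each has one factor wrong: time in the T1 model, stimulation in the trend model. The label matters because it tells the analyst which error term to use.

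The T1 model has a second fault. T0 is one of the two outcome levels and also the covariate, so half of the outcome rows are fixed by the covariate. Its stimulation main effect then averages a zero difference at T0 with the real difference at T1.

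These are statements in the text, not details left to an analysis plan. At stake are the size of the reported benefit and the validity of its test.

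**Working it through.** **Inputs.** From Sample size estimates: effect size 0.50 SD, SD 3.9 MFIS points, 63 per group, 80% power, no change under sham. From Statistical analysis: significance level 0.05, taken as two-sided because that reproduces 63 (one-sided would give 50). The MFIS correlation between visits, ρ, is not in the documents. It is assumed to be 0.3, 0.5 or 0.7, equal for all pairs of visits.

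**1. The plan's own figure.** n per group = 2(1.96 + 0.842)²/0.50² = 62.8, so 63, with power 0.801 under the normal approximation. This is an ordinary two-group comparison, and it reproduces.

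**2. Size of the estimate.** Let δ be the between-arm difference after treatment. Randomisation makes the expected difference at T0 zero.

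- T1 model, stimulation main effect: (0 + δ)/2 = δ/2. With δ = 0.50 SD this is 0.25 SD, or 0.975 instead of 1.95 MFIS points at SD 3.9.
- T1 model, time-by-stimulation term: δ − 0 = δ, the full 0.50 SD.
- T0–T4 model, stimulation main effect with a constant post-treatment effect: (0 + 4δ)/5 = 0.8δ.

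**3. Power of the T1 model with a participant-level error.** Regressing (T0 + T1)/2 on arm and T0 halves both the arm coefficient and its standard error relative to the ANCOVA of T1 on arm and T0. Regressing T1 − T0 on arm and T0 leaves both unchanged. The test statistic is the same in all three. Simulated power (4,000 runs, 63 per arm) is 0.82, 0.89 and 0.98 at ρ = 0.3, 0.5 and 0.7, with type I error about 5%.

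**4. T1 model with time taken literally as between-participant.** The two rows of each person are treated as independent, and one baseline slope is shared by both visits.

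- The pooled slope is (1 + ρ)/2, and the mean residual variance is (3 + ρ)(1 − ρ)/4.
- Model variance of the interaction: 4/n times that, or (3 + ρ)(1 − ρ)/n. True variance: 4(1 − ρ)/n. The ratio is (3 + ρ)/4.
- Type I error = 2[1 − Φ(1.96√ratio)].

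| ρ | Ratio | By formula | Simulated, 4,000 runs | Simulated, 20,000 runs |
|---|---|---|---|---|
| 0.3 | 0.825 | 7.5% | 8.0% | 7.3% |
| 0.5 | 0.875 | 6.7% | 7.1% | 6.6% |
| 0.7 | 0.925 | 5.9% | 6.7% | 5.9% |

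A random intercept alone does not mend this model while the slope is shared. The residual covariance of a person's two rows is −(1 − ρ)²/4, which is negative, so the intercept variance is estimated near zero. Letting baseline act separately at each visit returns the model to step 3.

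**5. T0–T4 model with stimulation taken literally as within-participant.** The variance of a five-visit mean is (1 + 4ρ)/5; the within-participant error implies (1 − ρ)/5. The ratio is (1 + 4ρ)/(1 − ρ), and type I error = 2[1 − Φ(1.96/√ratio)].

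| ρ | Ratio | Type I error | With participant random intercept |
|---|---|---|---|
| 0.3 | 3.14 | 27% | about 5% |
| 0.5 | 6.0 | 42% | about 5% |
| 0.7 | 12.7 | 58% | about 5% |

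**The case against.** The strongest defence is that both models are named as mixed models, and a competent analyst would fit them as such. In a classical repeated-measures ANOVA with the covariate acting at each visit, both the stimulation test and the time-by-stimulation test are numerically the T1 ANCOVA. In a linear mixed model with a participant random effect, software tests stimulation against participant-level variance whatever the text calls it. On that reading the inflated error rates never appear. This stands, and it makes those rates conditional. It does not rescue the wording, which contradicts the design, and it does not settle which of two estimates, 0.25 or 0.50 SD, is the treatment effect.

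A reader might infer more than the documents support:

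- **That both models use baseline twice.** Only the T1 model states a baseline covariate. T0 as an outcome level without that covariate, as in the trend model, is a legitimate analysis.
- **That halving the estimate costs power.** Power of 0.41, 0.36 and 0.33 at the three correlations belongs to a T0/T1 average without the covariate. The stated T1 model has the covariate.
- **That the trial was powered for the halved effect.** The power sentence speaks of a main effect, but the protocol also gives the time factor the name of the intervention. The same section refers to a single pairwise comparison, and 63 per group matches a plain two-group difference of 0.50 SD.

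**Conclusion.** The point holds as a fault in the stated analysis: one factor is mislabelled in each MFIS model, T0 has a double role in the T1 model, and no term is named as the treatment effect. The consequences are conditional.

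- **Certain from the algebra:** the T1 model's stimulation main effect is half the T1 effect. Its time-by-stimulation term is not, and halving by itself does not weaken the test when the covariate and a participant-level error are kept.
- **Only if the labels are executed literally:** type I error of about 6–8% for the T1 interaction, and about 27%, 42% and 58% for stimulation in the T0–T4 model. These rest on assumed visit correlations of 0.3, 0.5 and 0.7 and on equal correlation between visits. They should not be read as the error rates the trial will have.
- **Unaffected:** the 63 per group.

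Because this concerns the primary outcome and is cheap to repair, it should be corrected before analysis.

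**What to change.** 1. **T1 analysis.** ANCOVA of MFIS total at T1, with baseline MFIS as covariate and stimulation as the between-participant factor. Name the adjusted between-arm difference as the treatment effect.
2. **Trend analysis.** A linear mixed model with T1–T4 as outcomes and baseline MFIS as covariate, or T0–T4 as outcomes without that covariate. Visit is categorical and within-participant, stimulation is between-participant, with stimulation-by-visit and within-person correlation. Report the between-arm contrast at named visits.
3. **One primary result.** The ANCOVA and the mixed model's T1 contrast can differ when data are missing or when no baseline-by-visit term is included, so state which is primary. The Primary outcome measure section names no primary time point. T1 is used here because the first model addresses it; the sponsor should confirm it.
4. **Power sentence.** Reword Sample size estimates so that the 80% refers to the between-arm difference in MFIS at T1. The 63 per group stays.

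The cost is rewording of two sections. No extra participants or data are needed.

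### The T0–T4 mixed model, the only between-arm model stated for MFIS at T2–T4, uses baseline as an unconstrained response and so gives up precision that baseline adjustment would recover at no cost

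*Protocol article*

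**What the plan says.** The Statistical analysis section of the protocol article states two models for MFIS, each for the total score and the subscores.

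- **End of treatment (T1):** a "mixed-model analysis of variance with baseline MFIS scores as covariates, and the tDCS intervention (T0, T1) and stimulation (active, sham) as between-participant factors".
- **Follow-up:** the section introduces this model with "The trend of tDCS effects will be studied by entering the participants’ scores on the MFIS", and specifies a "linear mixed model with the tDCS intervention (T0, T1, T2, T3 and T4) and stimulation (active, sham) as within-participant factors". It names no baseline covariate, no stimulation-by-visit term and no restriction on the T0 means.

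The tests that come next do not compare the arms: "Pairwise comparisons between baseline and individual post-measurement-day significant results will conducted using Bonferroni t-tests for related samples". They set later visits against baseline within participants.

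The sample size section adopts an effect size of 0.50 and says "A sample size of 63 per group (a total of 126 participants) will give rise to 80% power in identifying the main effect of tDCS". On alpha, the analysis section says "The level of significance will be 0.05"; sidedness is not given.

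**The concern.** MFIS is measured at T0 in everyone, so a baseline-adjusted comparison is available at every later visit. The T1 model names such an adjustment and the follow-up model does not. Because the paired tests are within participants, any between-arm evidence that benefit lasts to 4 weeks has to come from the follow-up model.

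The issue is separate from the factor labels. Stimulation is called a within-participant factor although each participant receives one arm. If that is corrected, the model still has T0 as a free response in each arm. Its natural between-arm contrast at a follow-up visit is then a comparison of change scores, which is less precise than a covariate-adjusted comparison whenever rho is below 1. What is at stake is wider intervals and lower power at T2–T4 than the collected data allow.

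**Working it through.** **Inputs.** From the sample size section: effect size d = 0.50 and 63 per group. From the analysis section: alpha 0.05. Assumed: two-sided testing, equal SD at all visits, and rho, the correlation between T0 and the follow-up score. The article gives no rho for MFIS, so a range is shown.

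**The plan's own figure.** Two independent means, d = 0.50, 80% power, two-sided 0.05 gives 63 per group by the normal approximation (power 80.1%; 79.5% by noncentral t). The stated 63 reproduces.

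**Variance of the active-minus-sham contrast at one follow-up visit,** in units of SD² × 2/63:

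- T0 as a response with free means in each arm (difference in change): 2(1 − rho)
- Baseline as covariate, or T0 as a response with a common mean: 1 − rho²
- Ratio of adjusted to change-score variance: (1 − rho²) / [2(1 − rho)] = (1 + rho)/2, below 1 for every rho below 1

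**Power.** The noncentrality parameter is d × √(63/2) divided by the square root of the variance factor, with 124 degrees of freedom. At rho = 0.5:

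- Change: 0.50 × 5.612 / √1.00 = 2.806, power 79.5%
- Adjusted: 0.50 × 5.612 / √0.75 = 3.240, power 89.5%

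| rho | 2(1 − rho) | 1 − rho² | (1 + rho)/2 | Power, change | Power, adjusted | Gain (points) |
|---|---|---|---|---|---|---|
| 0.3 | 1.40 | 0.91 | 0.65 | 65.3% | 83.1% | 18 |
| 0.4 | 1.20 | 0.84 | 0.70 | 72.0% | 86.0% | 14 |
| 0.5 | 1.00 | 0.75 | 0.75 | 79.5% | 89.5% | 10 |
| 0.6 | 0.80 | 0.64 | 0.80 | 87.6% | 93.6% | 6 |
| 0.7 | 0.60 | 0.51 | 0.85 | 94.9% | 97.4% | 2.5 |
| 0.73 | 0.54 | 0.467 | 0.865 | 96.6% | 98.3% | under 2 |

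**Simulation check.** Five visits, 63 per arm, compound symmetry. At rho 0.5 the empirical standard errors, in SD units, were 0.175 for the change contrast and 0.151 for the adjusted one (theory 0.178 and 0.154). At rho 0.7 they were 0.136 and 0.127 (theory 0.138 and 0.127). With T0–T4 as responses and free arm-by-visit means, the fitted contrast equalled the difference in change exactly.

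**Would copying the T1 covariate across be enough?** No. With T0 kept as an unconstrained response and baseline MFIS added as a main-effect covariate, the stimulation-by-visit contrast did not move (largest difference about 2 × 10⁻¹⁵). A covariate that is constant within a participant cancels from a contrast between visits. T0 has to leave the response, or its mean has to be common to the arms.

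**The case against.** **Baseline is already used.** A reader might infer that the model ignores baseline, or leaves chance baseline imbalance in the estimate. The text does not support that. T0 is a response level, and the change contrast subtracts each arm's baseline mean. This also fits the Abstract, which defines the primary outcome as a change in severity. Leaving out a covariate when baseline is already a response is ordinary practice. This objection stands, and it confines the point to efficiency.

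**The form is not fully fixed.** The article states neither free T0 means nor an interaction, and a common T0 mean would lose nothing. That is so, but the article states no such constraint, and the listed factors fitted in the usual way give the less efficient version. The point concerns the model as listed, not a missing detail.

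**The size is uncertain.** No rho is given. The one reliability figure shown, an intraclass correlation of 0.73–0.93 in the Baseline measures section, would put the gain under 2 points. It belongs to the FSS, not the MFIS, so it does not settle rho; nothing in the article supports 0.5 either.

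**Two conflicting T1 results?** A reader might infer that the two models must report different T1 effects. They need not. The T1 model also keeps T0 as a level, so its stimulation-by-time contrast is a difference in change too. With missing visits filled by carrying the last observation forward, both models give the same contrast. They differ only if the T1 model is read through its stimulation main effect, where the covariate does act. For the same reason the T1 model is not a good standard for judging the follow-up model.

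**Is the sample size undermined?** A reader might link the power statement's reference to a main effect to the T0–T4 model. The sample size section ties its power to a single pairwise comparison in an analysis of variance, not to T2–T4, so that link is not supported.

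**Conclusion.** The point holds as one of lost precision in the follow-up comparison. As listed and fitted without constraint, the T0–T4 model needs a variance larger by a factor of 2/(1 + rho) than an adjusted analysis of the same data: one third larger at rho 0.5 (2/1.5 = 1.33). The power given up is about 18 points at rho 0.3 and 10 at 0.5. It is at least 5 points only up to rho of about 0.6, and under 2 above about 0.73. These figures assume equal SDs, a true effect of 0.50 SD at the visit, 63 analysed per group and two-sided testing. No bias or invalid inference is shown, and the 63 per group stands. Because the gain costs nothing, the change is worth making even though rho is unknown.

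**What to change.** Before unblinding, replace the follow-up model sentence with one of these:

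1. Responses T1, T2, T3 and T4; visit as within-participant factor; stimulation as between-participant factor; stimulation-by-visit; baseline MFIS (the matching baseline subscore for each subscore) and baseline-by-visit as covariates.
2. Responses T0–T4 with visit and stimulation-by-visit, the two arms constrained to a common T0 mean.

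Report the baseline-adjusted active-minus-sham difference with its interval at each visit, and take the T1 estimate from the same model in place of the separate T1 analysis. Do not simply add baseline as a covariate while T0 remains an unconstrained response.

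The cost is one sentence of analysis wording, with no new data, visits or participants. Participants with only an observed T0 score contribute nothing under option 1 unless a later value is imputed; option 2 keeps them.
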